### Analysis

Descriptive statistics (means ± SD or median and inter quartile range as appropriate) will be used to describe the study sample with regard to demographics and baseline (clinical) characteristics. On the basis of an intention-to-treat analysis, differences in changes between the intervention group and control group are calculated with 95% confidence intervals at 3, 6 and 12 months for both primary and secondary outcomes.

Using *t*-tests and multiple linear regression – duly adapted for the multilevel structure of the data – we will compare changes in HbA1c, number of hypoglyceamias, quality of life, treatment satisfaction, illness and insulin perceptions and confidence in diabetes self-care scores at different time intervals between the groups, with adjustment for important prognostic factors like age, diabetes duration, medication and level of education where appropriate. Separate analyses of possible effect modifiers (i.e. age, depression, previous internet use) will be performed in order to gain a better understanding as to who benefits most from the intervention.

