#### Primary outcome measure

The primary outcome measure is the difference in change in glycaemic control (HbA1c) between intervention and control group. HbA1c will be measured at baseline, 3 and 12 months. The measurement of HbA1c at 6 or 9 months will take place only if HbA1c is still above 7% at 3 respectively 6 months.

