### Sample size calculation

The sample size is calculated to detect a clinical relevant difference of 0.5% in HbA1c between groups. In the Diabetes Care System West-Friesland the standard deviation (sd) of HbA1c of the general diabetes population is 1.2% [49]. A difference (d) between the intervention and control group in changes of 0.5%, a standard deviation (sd) of 1.2%, an alpha of 0.05 (two-sided), and a power of 80%, the number of patients requested in each group is 90.

Because cluster randomisation is applied at the level of general practices, the number of patients has to be multiplied with the following formula: 1 + (k-1)ρ, in which ρ is the intercorrelation coefficient (ICC) between practices. The ICC is statistically determined to be 0.05. k is the number of patients per practice that will join the study. Based on our experience, we estimate that 4 patients per practice will make the transition to insulin treatment in one year and meet the criteria of our trial. A participation of 26 general practices is needed per group:

Furthermore, taking into account a possible dropout rate of 15%, the total number of practices needed is: 2 * 26/(1–0.15) = 62, which means that 248 patients will be required.

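### The primary HbA1c comparison has no named time point, so the single 5% test behind the sample size is not secured

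*Protocol article*

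**What the plan says.** Four places in the protocol article could fix when the primary outcome is judged: the Abstract, the Objectives, the Primary outcome measure section and the Sample size calculation. All describe an effect on HbA1c or on its change, and none attaches a month to it.

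On measurement, the Primary outcome measure section states: "HbA1c will be measured at baseline, 3 and 12 months". It adds that a 6-month or 9-month value is taken only in patients whose HbA1c was still above 7% at the preceding check (3 or 6 months respectively).

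The Sample size calculation budgets one comparison: "A difference (d) between the intervention and control group in changes of 0.5" percentage points, with "an alpha of 0.05 (two-sided), and a power of 80%, the number of patients requested in each group is 90".

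The Analysis section then says, on an intention-to-treat basis, that between-group differences in change "are calculated with 95% confidence intervals at 3, 6 and 12 months for both primary and secondary outcomes". It goes on to compare changes at several intervals by t-tests and multiple linear regression adapted for the multilevel structure. It gives no order among the times and no rule for what counts as success. The Setting section describes the article as the definitive study protocol.

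**The concern.** The time point is part of the definition of a primary outcome. Here the design pays for one test, and the analysis puts three comparisons of the same primary outcome side by side. Nothing tells a reader which of them decides the trial.

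A difference at 3 months that had gone by 12 months could be reported as the primary result, and so could the reverse. Nothing in the article would contradict either report. The 0.5-point target is likewise tied to no time. This matters because the Discussion speaks of improving and sustaining control, and links a positive result to wide use of the programme in Dutch general practice.

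**Working it through.** **1. Reproduce the plan's figure.** Inputs from the Sample size calculation: difference 0.5; "the standard deviation (sd) of HbA1c of the general diabetes population is 1.2"%; two-sided alpha 0.05; power 80%; ICC 0.05; 4 patients per practice; 15% dropout.

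- Per group before clustering: 2 × [1.2 × (1.960 + 0.842) / 0.5]² = 90.4; the plan states 90.
- Design effect: 1 + (4 − 1) × 0.05 = 1.15.
- Practices per group: 90 × 1.15 / 4 = 25.9, so 26.
- Total: 2 × 26 / 0.85 = 61.2, so 62 practices; 62 × 4 = 248 patients.

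The figure reproduces, and it rests on one test at two-sided 5%.

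**2. Which times are measured in everyone.**

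| Time | Who has an HbA1c value | Listed for the primary comparison |
|---|---|---|
| 3 months | all patients | yes |
| 6 months | only those above 7% at 3 months | yes |
| 12 months | all patients | yes |

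Only 3 and 12 months allow a comparison of all randomised patients.

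**3. False-positive rate if significance at any one time counted as success.** This rule is an assumption, since the article states none. For independent tests the rate is 1 − 0.95² = 9.75% with two times and 1 − 0.95³ = 14.3% with three. Repeated HbA1c comparisons are correlated, but the article gives no correlation, so a range is shown. The rates come from 1,000,000 simulated sets of equally correlated normal test statistics, counting any |z| above 1.96.

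| Assumed correlation | 3 and 12 months | 3, 6 and 12 months, 6 treated as a full-sample test |
|---|---|---|
| 0.3 | 9.5% | 13.6% |
| 0.5 | 9.1% | 12.6% |
| 0.7 | 8.3% | 10.9% |
| 0.8 | 7.8% | 9.9% |
| 0.9 | 7.0% | 8.4% |

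The middle column is the supportable one. The right-hand column is for reference only: the 6-month comparison uses a subset selected after randomisation, and neither its size nor its correlation with the other comparisons is known.

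**4. The opposite rule.** If significance in the same direction were required at both 3 and 12 months, the same simulation gives 0.47% at correlation 0.3 and 2.95% at 0.9, below 5%. The error rate therefore depends on a decision rule that the article does not state.

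**The case against.** The strongest reply is that the article nowhere says a positive result at any time would be a success. It says that intervals are calculated and changes compared. Multiplicity rules are commonly left to a statistical analysis plan, which may exist and is not shown. This stands in part. The lack of a multiplicity rule is not itself a fault, and the inflation is conditional. But the time point belongs to the outcome definition. The Analysis section is also not silent on it: it lists three times on an equal footing.

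A reader might infer that the 5% level is definitely broken, or that the error rate is 8.4% to 13.6% from three tests. The documents support neither. The first needs a success rule that is not written. The second treats the 6-month comparison as an ordinary test in all patients, which the measurement schedule rules out.

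A reader might also count the t-tests and the regression as further multiple testing. Unadjusted and adjusted analyses of the same change are usually highly correlated and are often reported together. They leave some doubt about which is primary, but they add nothing to the rates above.

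**Conclusion.** The concern holds in a limited form. The primary outcome has no primary time point, three times are listed without priority, and one 5% test is budgeted. The 5% level is not secured. This is weaker than saying that it fails.

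For the two times measured in everyone, reading significance at either as success would give about 7.0% to 9.5%, for assumed correlations of 0.9 to 0.3. For any correlation below 1 the rate exceeds 5%. The figures also assume that each test on its own holds its nominal level.

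Separately, the 6-month comparison cannot be a co-equal intention-to-treat primary comparison, whatever rule is chosen. The sample-size arithmetic is not in question.

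**What to change.** Amend the Primary outcome measure, Sample size calculation and Analysis sections together:

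- Name change in HbA1c at one time point measured in all patients as the single primary comparison, and tie the 0.5-point target to it. Twelve months fits the aim of sustained control in the Discussion; the investigators could justify 3 months.
- Test it once, at two-sided 0.05, with one named multilevel regression. Preferably add baseline HbA1c as a covariate. This would be new: the Analysis section gives age, diabetes duration, medication and education as examples of adjustment factors and does not name baseline HbA1c.
- Label the other times and the t-tests secondary or supportive.

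The trial began in January 2009 with first results expected in 2011, so the change should be a dated amendment made before any comparative data are seen. It costs short edits in three sections. It needs no new visits or measurements, and 62 practices and 248 patients stand.

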### Objectives

The primary objective of the study is to determine the effect on glycaemic control (HbA1c) of a patient-centred web-based insulin-titration programme in suboptimal controlled T2DM patients starting insulin treatment.

Secondary objectives are to assess the effects of the intervention on frequency of hypoglycaemic episodes, illness perceptions, self-efficacy, treatment satisfaction, and quality of life.

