### Study population

The target population consists of T2DM patients (35–75 years) from general practitioners with suboptimal controlled glucose (i.e. HbA1c ≥ 7.0%) and maximal oral hypoglycaemic agents, not using insulin. Inclusion and exclusion criteria are listed in Table 1.

**Table 1 T1:** Inclusion and exclusion criteria

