#### Intervention group

When informed consent is given, patients in the intervention group will receive individual education on diabetes in general, all aspects of insulin treatment, the use of a self-monitoring device, the importance of self-monitoring, and aspects of hypo- and hyperglycaemia. In addition, information about diabetes in general and its management is available on the trial website (provided by [38]), an online education programme developed by the University of Maastricht and the Academic Hospital Maastricht, the Netherlands). The education will be given in two sessions (with an interval of 1 or 2 weeks) by the GP or practice nurse in general practices using a standard protocol provided by the investigators. The patients will receive a manual how to use the internet programme.

The internet programme is accessible through a log-in procedure, requiring a log-in name and a password. The programme is not accessible for the control group or others without permission. In case of problems, patients can always contact their practice nurse or GP, who do have access to the online data of their patients.

Patients will start with 10 IE insulin glargine. The next day, a patient has to log-in in order to start the internet programme, that consists of an online-diary with computerized algorithms. Feedback will be given on fasting blood glucose (FBG) measurements that have to be completed in the diary. The programme will reply with an insulin dose advice when two FBG measurements (on two successive days) are inputted (+ 4 IE when FBG exceeds 10 mmol/l for 2 consecutive days; + 2 IE when FBG is between 7–10 mmol/l for 2 consecutive days; – 2 IE when FBG is between 2.5–4 mmol/l for 2 consecutive days; – 4 IE when FBG is below 2.5 mmol/l for 2 consecutive days). In case of a high or low FBG level, the programme will also respond with a feedback question, guided by the self-regulation theory. According to the patients' answer, advice will be given on the concerning item (e.g. adjustment of diet or increase of physical activity). Feedback will also be given visually in colours, tables and graphics.

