#### Control group

Patients in the control group will receive individual instructions with regard to insulin dose-adjustments from their GP or practice nurse as usual. The number or type of contacts might differ per practice. The titration scheme of insulin glargine will be determined by the GP or practice nurse. Because there is no strict regimen, this can also differ per practice. The patients are offered access to the information provided on the trial website and for completing the web-based questionnaires only. GPs or practice nurses can contact a diabetes nurse from the Diabetes Research Center concerning questions about the insulin therapy.

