#### Secondary outcome measures

The following secondary outcomes will be assessed in web-based self-administered questionnaires:

• Quality of life is assessed with the 12-item Short Form Health Survey (SF-12) [39], measured at baseline and after 3 and 12 months. The EuroQol (EQ-5D) [40] will be administered at baseline and after 3, 6 and 12 months. This questionnaire assessing the current health status consists of 5 dimensions (mobility, self-care, usual activities, pain/discomfort, and anxiety/depression), each with 3 levels.

• Treatment satisfaction is assessed with the Diabetes Treatment Satisfaction Questionnaire status and change version (DTSQs and DTSQc) [41-44]. The 8-item questionnaires, measure treatment satisfaction and how this satisfaction has changed on 7-point Likert scale. It will be used as an evaluation instrument of the intervention and will be measured at baseline, 3 and 12 months.

• Self-efficacy beliefs are assessed with the Confidence in Diabetes Self Care. This is a 21-item questionnaire, measuring the level of confidence a diabetes patient has in performing self-care activities on 5-point Likert scale [45]. It will be measured at baseline, 3, 6 and 12 months and will be used in evaluating the theoretical background.

• Illness perceptions are assessed with the brief Illness Perception Questionnaire (brief-IPQ). This is a 9-item questionnaire assessing the five core dimensions of illness representations (illness identity, timeline, personal control, treatment control, cause) according to Leventhal's theory of self-regulation [46]. It will be measured at baseline, 3, 6 and 12 months to determine changes in patients' representations regarding diabetes and its controllability and will also be used in evaluating the theoretical background.

• The patient-reported number of hypoglycaemias will be measured by means of a hypoglycaemia diary in which the patient report the severity of each event, glucose value, self-treatment and need of assistance.

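### The number of hypoglycaemias is to be analysed as a change by t-test and linear regression, although it is a diary event count with no stated baseline and unequal observation time

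*Protocol article*

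**What the plan says.** The protocol article treats hypoglycaemia in four places.

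- **Objectives.** It is a secondary objective, worded as a rate-like quantity: "Secondary objectives are to assess the effects of the intervention on frequency of hypoglycaemic episodes". The Abstract also speaks of frequency.
- **Secondary outcome measures.** It is defined as a count: "The patient-reported number of hypoglycaemias will be measured by means of a hypoglycaemia diary". Severity, glucose value, self-treatment and need of assistance are recorded for each event. No baseline period and no counting window are given. Each questionnaire outcome in the same list has a baseline; for self-efficacy, for example, "It will be measured at baseline, 3, 6 and 12 months and will be used in evaluating the theoretical background".
- **Study population.** Patients enter on "maximal oral hypoglycaemic agents, not using insulin", so any count before the intervention would be a count before insulin.
- **Analysis.** Differences in changes between the arms are to be given "at 3, 6 and 12 months for both primary and secondary outcomes". The methods named are t-tests and multiple linear regression, adapted for clustering, and with them "we will compare changes in HbA1c, number of hypoglyceamias, quality of life, treatment satisfaction", followed by the perception and self-care scores.

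The Sample size calculation allows for 15% dropout overall.

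**The concern.** The stated method suits HbA1c and the questionnaire scores, which are measured at baseline and again at fixed times. It does not suit an event count built up over follow-up.

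There are two separate problems. First, a change needs a starting value, and none is planned for the diary in the article. Second, a patient who leaves after three months has had a quarter of the time in which to record events. A t-test or linear model on raw counts reads that short record as a low count. Adapting the model for clustering does not deal with this.

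Hypoglycaemia is the only adverse-event outcome among the primary and secondary outcomes, and the trial hands insulin titration to the patient. If the self-titration arm had the shorter follow-up, an excess of events in that arm would be understated.

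**Working it through.** **1. The plan's own figure.** The article gives no calculation for hypoglycaemia. Its sample size rests on HbA1c and reproduces:
- 2 × (1.2 × (1.960 + 0.842) / 0.5)² = 90.4 per group (stated 90)
- design effect 1 + (4 − 1) × 0.05 = 1.15
- 90 × 1.15 / 4 = 25.9, so 26 practices per group
- 2 × 26 / 0.85 = 61.2, so 62 practices and 62 × 4 = 248 patients, or 124 per arm

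Nothing below alters this.

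**2. Bias of raw counts, by arithmetic.** Assume that a fraction d of an arm drops out at times spread evenly over the year, and that the event rate is constant. Mean observation time is then 1 − d/2 years, and the expected raw-count ratio is the true rate ratio × (1 − d₁/2) / (1 − d₀/2), with 1 for intervention and 0 for control.
- Dropout 15% in both arms: 0.925 / 0.925 = 1, so no bias.
- Dropout 5% control, 25% intervention (15% overall): 0.875 / 0.975 = 0.897. A true ratio of 1 appears as 0.90, and a true 1.5 as 1.5 × 0.897 = 1.35.
- The reverse split: 0.975 / 0.875 = 1.11, so the bias changes direction.

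**3. Error rate and power, by simulation.** The inputs are 124 patients per arm (from the article) and gamma-Poisson counts with a control rate of 1 or 4 events a year and dispersion 1 or 3. Dropout times are as in step 2. There were 600 runs per scenario, and clustering was ignored. Event rates, dispersion and the split of dropout by arm are assumptions, since the article gives none. A Welch t-test on raw counts was set against negative binomial regression with a log-exposure offset. The ranges are over the four combinations of rate and dispersion.

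| Dropout, control / intervention | True ratio | t-test rejects | Rate model rejects | Median raw ratio | Median rate-model ratio |
|---|---|---|---|---|---|
| 15% / 15% | 1 | 4.0–5.0% | 4.4–5.5% | 0.98–1.01 | 0.98–1.00 |
| 15% / 15% | 1.5 | 35.2–77.7% | 39.0–82.3% | 1.49–1.55 | 1.49–1.54 |
| 5% / 25% | 1 | 6.2–12.2% | 4.2–5.7% | 0.88–0.91 | 0.97–1.01 |
| 5% / 25% | 1.5 | 19.3–49.8% | 35.9–82.2% | 1.33–1.36 | 1.49–1.50 |

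With equal dropout, the power gaps in the four combinations are 1.9, 3.2, 4.6 and 3.8 points. With 5% v 25% they are 24.7, 16.6, 32.4 and 21.2 points. The simulated raw ratios agree with the arithmetic in step 2.

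**4. Skew alone.** The share of patients with no event over a full year is (1 + dispersion × mean)^(−1/dispersion). For the four control-arm settings this is 0.50 (rate 1, dispersion 1), 0.63 (1, 3), 0.20 (4, 1) and 0.43 (4, 3). Even so, the t-test kept its error rate under equal dropout. The difficulty is observation time, not zeros.

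**The case against.** The best defence is that the harm depends on an imbalance that the article does not predict. It gives a single overall dropout figure and no reason to expect more loss in one arm. With equal dropout the t-test is nearly as good as the rate model. This stands, and it limits the size of the point.

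It can also be said that the full protocol may define a baseline diary period, that the Analysis section compares outcomes over different time intervals (which allows counts per interval), and that the word changes may grammatically attach to HbA1c alone. Part of this stands: a missing diary schedule would not by itself be a finding. But the article fixes the method. The sentence before applies differences in changes to all secondary outcomes, and on either reading the t-test and linear model cover the count.

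Four stronger readings are tempting, and the article does not support them.

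- **That a change in hypoglycaemias cannot exist.** Patients enter on maximal oral agents, and the Discussion names SU-derivatives among those that may be continued, so a pre-insulin count is conceivable. What can be said is that no baseline count is stated.
- **That this is the trial's main safety comparison.** The article ranks it as one of several secondary outcomes and claims no power for it.
- **That skewed counts cost the t-test much power.** At 124 per arm, under the assumed rates, they do not.
- **That more intensive monitoring inflates the intervention count.** A reader might set "Feedback will be given on fasting blood glucose (FBG) measurements that have to be completed in the diary" against "Because there is no strict regimen, this can also differ per practice". The second sentence concerns the titration scheme, not glucose monitoring. All patients must be able and willing to self-monitor, and intervention patients on a stable dose are advised to measure once a week. The online glucose diary is also described separately from the hypoglycaemia diary. No monitoring frequency is given for the control arm, so no size can be attached to this.

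**Conclusion.** The point holds: the named method does not match the outcome as the article defines it. No baseline count is stated from which to take a change, and raw counts disregard unequal observation time. It should be corrected, but as planned it is not fatal to the comparison.

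With equal dropout the loss is small: about 2 to 5 points of power, with type I error intact. If dropout differs between arms, the comparison is biased towards fewer events in the arm with less follow-up. At 5% v 25%, a true ratio of 1 appears as about 0.88 to 0.91 and a true 1.5 as about 1.33 to 1.36. Type I error is then 6–12%, and power falls by roughly 17 to 32 points against the rate model.

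These figures rest on assumed event rates, dispersion and dropout split, on a constant event rate, on dropout unrelated to hypoglycaemia, and on ignoring clustering. The direction of the bias follows from the arithmetic; its size in this trial is unknown.

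**What to change.** In the Analysis section, take hypoglycaemia out of the outcomes compared as changes, and state instead:

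- **Outcome:** number of diary events from insulin start to 12 months.
- **Model:** negative binomial regression with log diary time as offset. The randomised cluster (general practice, or practice nurse with the attached practices) enters as a random effect, or GEE is used.
- **Report:** rate ratio with 95% confidence interval, with events and diary time by arm.
- **Supportive breakdown:** events by recorded severity and need of assistance, without redefining the outcome.

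The offset corrects for length of observation, not for dropout that is itself related to hypoglycaemia, so dropout by arm should be shown beside the result.

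The cost is slightly more analysis work, plus a record of the dates each diary covers. No further patients are needed, and the 248-patient calculation is unaffected.

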### Randomisation and treatment allocation

General practices will be randomly assigned to the intervention or control group using a computerized randomisation programme. In case a practice nurse takes care of the insulin titration (working for one or more general practices), the practice nurse will be randomised and corresponding general practice(s) will be allocated to one of the groups. It is desirable that the two groups will be similar with regard to the amount of patients in each group. For that reason we will apply stratified randomisation [34]. Clusters with one or two general practices and clusters with three or more general practices will be randomised separately. Randomisation will be performed by the manager of the website company (Curavista B.V., Geertruidenberg, the Netherlands), who is independent of the patients and their care. Patients in the intervention group will self-adjust the insulin dose supported by an internet programme and receive education before starting insulin. The control group will receive physician-driven (GP or practice nurse) adjustments, i.e. the GP or practice nurse will perform the insulin titration in his/her own manner, guided by guidelines from the Dutch College of General Practitioners.

When a patient is eligible to participate in our study the GP or practice nurse will provide a letter of invitation and an information brochure of the trial based on the assigned group. The next visit will be scheduled one week later in which the patient can give his or her informed consent to participate in the trial.

The flow of the patients is registered by the investigator (MR), according to a flow diagram recommended by the CONSORT statement and its extended version to cluster randomised trials [35,36]. Reasons for withdrawal are registered by the practice nurse or GP. Figure 1 shows the design of the study.

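### The primary comparison is of HbA1c changes, and the open covariate list does not commit to baseline HbA1c, although adjusting for it would cost nothing and improve precision

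*Protocol article*

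**What the plan says.** The protocol article, Primary outcome measure, defines the endpoint as a change: "The primary outcome measure is the difference in change in glycaemic control (HbA1c) between intervention and control group". The same section confirms that the starting value is collected: "HbA1c will be measured at baseline, 3 and 12 months".

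The Analysis section carries this through. Using t-tests and multiple linear regression that allow for clustering, "we will compare changes in HbA1c, number of hypoglyceamias, quality of life, treatment satisfaction" and further questionnaire scores, "with adjustment for important prognostic factors like age, diabetes duration, medication and level of education where appropriate". The Discussion adds co-medication as a possible confounder or effect modifier. Baseline HbA1c is not named as a covariate in any section.

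Two design features in Randomisation and treatment allocation bear on this. Randomisation is stratified by cluster size: "Clusters with one or two general practices and clusters with three or more general practices will be randomised separately". Patients enter after their practice has been allocated, when the GP or practice nurse "will provide a letter of invitation and an information brochure of the trial based on the assigned group". The Blinding section says that these providers cannot be blinded.

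The Sample size calculation uses "A difference (d) between the intervention and control group in changes of 0.5" per cent, and states that "the standard deviation (sd) of HbA1c of the general diabetes population is 1.2" per cent.

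**The concern.** A change score fixes the coefficient of baseline at 1. If the true regression slope of follow-up on baseline is below 1, two things follow. The comparison carries more residual variance than a model that estimates the slope. And an arm that happens to start higher is expected to fall further whatever its treatment, so part of any baseline difference remains in the estimated effect.

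Imbalance is more plausible here than in an individually randomised trial with concealed allocation. Practices are allocated first, and unblinded staff then invite patients with arm-specific material.

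The wording also leaves the covariate set for the primary comparison to be settled later, and it names two methods. One of them, the t-test on change, has no place for a baseline covariate. At stake are the width of the primary confidence interval and how robust the estimate is to a chance difference in starting HbA1c.

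**Working it through.** **Inputs from the protocol article (Sample size calculation).** Target difference 0.5; SD 1.2; two-sided alpha 0.05; power 80%; 90 patients per group before clustering; ICC 0.05; 4 patients per practice; 26 practices per group; dropout 15%; 62 practices; 248 patients.

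**Assumptions not in the document.** The baseline to follow-up correlation r, the slope of follow-up on baseline, and the size of a baseline difference between arms. The SD of 1.2 comes from a general diabetes population, so applying it to these patients is also an assumption.

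**Step 1: the plan's own figure.** n per group = 2 × [1.2 × (1.960 + 0.842) / 0.5]² = 90.4 (stated: 90). Design effect = 1 + 3 × 0.05 = 1.15. 90 × 1.15 / 4 = 25.9, so 26 practices per group. 2 × 26 / 0.85 = 61.2, so 62 practices and 62 × 4 = 248 patients. The figure reproduces and takes no credit for baseline adjustment.

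**Step 2: precision.** With equal SD σ at both times:
- variance of change = 2σ²(1 − r)
- residual variance after baseline adjustment = σ²(1 − r²)
- ratio = (1 + r)/2, which is below 1 for every r < 1.

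If the SDs differ (σ_b at baseline, σ_f at follow-up), the change-score variance minus the adjusted variance is (σ_b² + σ_f² − 2rσ_bσ_f) − σ_f²(1 − r²) = (σ_b − rσ_f)². This is never negative. The direction therefore does not depend on equal SDs; the exact ratio does.

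**Step 3: power.** With 26 × 4 = 104 evaluable per arm, the effective n is 104 / 1.15 = 90.4. Power = Φ(0.5 / (s√(2/90.4)) − 1.96), where s is the relevant SD and the design effect is taken as the same for both analyses. The document can be read two ways. Reading A takes 1.2 as the cross-sectional SD of HbA1c, as described. Reading B takes it as the SD of change, as it is used.

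| r | Variance ratio | Reduction in SE | A: change only | A: adjusted | B: change only | B: adjusted |
|---|---|---|---|---|---|---|
| 0.2 | 0.60 | 22.5% | 60.1% | 81.6% | 80.0% | 95.1% |
| 0.3 | 0.65 | 19.4% | 65.8% | 83.6% | 80.0% | 93.5% |
| 0.5 | 0.75 | 13.4% | 80.0% | 89.9% | 80.0% | 89.9% |
| 0.7 | 0.85 | 7.8% | 95.1% | 97.5% | 80.0% | 86.0% |
| 0.8 | 0.90 | 5.1% | 99.3% | 99.7% | 80.0% | 84.0% |

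Under A, unadjusted change reaches 80% only when r is about 0.5 or more.

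**Step 4: baseline difference.** Shift in the change-score contrast = (1 − slope) × baseline difference. For an assumed difference of 0.3:
- slope 0.3: 0.7 × 0.3 = 0.21, or 42% of the 0.5 target
- slope 0.5: 0.5 × 0.3 = 0.15, or 30%
- slope 0.7: 0.3 × 0.3 = 0.09, or 18%.

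The standard error of a chance baseline difference at effective n 90 is 1.2 × √(2/90) = 0.18. A difference of 0.3 is thus about 1.7 standard errors, reached in either direction in about 9% of trials.

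**The case against.** The strongest reply is that failing to name a covariate does not exclude it. The list is introduced by example and closes with a discretionary qualifier. Regressing change on arm and baseline HbA1c gives the same arm coefficient as regressing follow-up on both, so the planned regression can already accommodate the adjustment. An article also commonly leaves the exact covariate set to an analysis plan. This stands to the following extent: a reader might infer that the plan rules out baseline adjustment and necessarily leaves imbalance uncorrected, and the document does not support that. But the article is not silent on the matter. It selects change, selects the methods and names four covariates, and one of the two methods cannot adjust for baseline.

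Other objections also limit the point:
- Regression to the mean from the entry threshold of HbA1c ≥ 7.0% acts on both arms. It distorts the contrast only if the baselines differ.
- Only the fraction (1 − slope) of a baseline difference passes into the estimate, not all of it.
- If arms differ through selective recruitment rather than chance, neither analysis is guaranteed unbiased. Baseline adjustment does not cure selection on unmeasured factors.
- At high r the gain is small.
- The stratum was introduced to balance patient numbers, and its prognostic value is not given. Leaving it out would usually make the standard error somewhat conservative rather than bias the estimate.
- Region is not a randomisation factor, so the design gives no reason to require it as a covariate.

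**Conclusion.** The point holds as an improvement to the stated primary comparison. Baseline HbA1c should be a fixed part of the primary model, and at present nothing commits to it. With equal SDs, adjustment cuts the variance by 40% at r = 0.2, 25% at r = 0.5 and 10% at r = 0.8. It also removes the part of the estimate that follows linearly from a measured difference in starting HbA1c: 0.09 to 0.21 for an assumed 0.3-point difference and slopes of 0.7 to 0.3. The values of r, slope and imbalance are assumptions; the direction of the precision gain is not.

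A reader might go on to infer that the trial is too small. The document does not support that. The stated size reproduces, and if 1.2% serves as the SD of change, planned power is 80% without adjustment and higher with it. Only if 1.2% is the cross-sectional SD and r is below about 0.5 does the unadjusted comparison fall short. Which SD is meant is a separate question.

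**What to change.** In the Analysis section, name a single primary model: a multilevel regression of HbA1c (follow-up or change) on arm, with baseline HbA1c as a prespecified fixed covariate and the randomised cluster (practice or practice nurse) as a random effect. Remove the discretionary qualifier for the baseline term, and do not let a t-test on change serve as the primary analysis.

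As a secondary point, include the cluster-size randomisation stratum as a fixed term, mainly so that the standard error reflects the stratified design. Adjust each questionnaire score for its own baseline value.

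The cost is a change of wording. Baseline HbA1c and the stratum are already known for the trial, and neither the sample size nor any procedure has to change.
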